### Intervention

A brief summary of the adaptation and optimisation of the PLH programme in phases 1 and 2 of the FLOURISH project is provided in online supplemental appendix 3 and described in Shenderovich *et al* and Piolanti *et al*.^30
31^ Below, we provide an overview of the version of the PLH programme that will be evaluated in phase 3.

Intervention group: Adapted PLH programme. The adapted PLH programme is designed to address key developmental and psychosocial needs by enhancing adolescents’ and caregivers’ communication, problem-solving and emotion regulation skills and strengthening family relationships, with the goal of preventing violence and improving positive parenting practices, ultimately benefiting mental well-being of adolescents and caregivers. It will be delivered over 7 weeks including a preprogramme visit and 6 weekly group sessions, each lasting approximately 2 hours, to groups of 10 adolescent–caregiver pairs. All sessions start and end jointly, and some sessions will also be completely conducted jointly, while parts of other sessions will be held separately for adolescents and caregivers to facilitate open discussion. Each group will be led by two facilitators who complete training on the PLH programme and receive ongoing supervision informed by video recordings to ensure fidelity. Supervisors also participate in trainings focused on supervision techniques and the use of the PLH Facilitator Assessment Tool (PLH-FAT).^36
37^ Session formats and content are detailed in table 2. Between-session home practice activities are included to support skill reinforcement. Programme materials for families and facilitators are freely available in English, Macedonian, Romanian, Russian and Ukrainian, and can be accessed through the FLOURISH website: https://www.flourish-study.org/study-materials.html. For participants who miss a group session, brief catch-up sessions are available.

**Table 2 T2:** Adapted PLH programme

Week	Session	Adapted PLH programme for parents and teens	Content examples
1	0	Preprogramme visits	Introduction to the PLH programme for caregivers and teens
2	1	Developmental stages*	Introduction round Group rules House of support Biological, psychological and social changes during adolescence
3	2	Building a positive relationship through spending time together†	Quality time, trust and praise in family relationships
4	3	Talking about emotions and sensitive topics*	Dealing with positive and negative emotions I-statements Setting rules for speaking and listening
5	4	What do we do when we are angry*	Anger and stress management strategies Reframing thoughts
6	5	Establishing rules and routines†	Role play: importance of rules and routines Setting rules and routines and practice them
7	6	Problem solving*	5 steps to solve problems Saying no Celebration

* Separate session parts for adolescents and caregivers.

† Joint sessions with adolescents and caregivers.

To encourage participation, adolescents and caregivers receive a €5–€10 voucher (in local currency) after each assessment. In the final session, participants will also receive a certificate of attendance (for participation in fewer than five PLH sessions) or a certificate of successful completion (for attending five to six PLH sessions).

Control group: Waitlist control condition. The waitlist control group will receive the adapted PLH programme after the intervention group has completed the 6-month post-baseline assessment.

### Data collection and outcomes

Participants will be assessed at three time points: baseline, post-intervention (8–12 weeks after baseline) and at follow-up (6 months after baseline assessment) using computer-assisted self-administered questionnaires completed on tablets, computers or smartphones. Paper-based versions will be provided if necessary. Adolescents and caregivers will complete assessments separately, supported by trained data assessors. Assessors will receive training in data collection procedures, safety protocols and the monitoring and reporting of adverse events (AEs). All measures not previously available in the study languages were culturally adapted, translated and tested using a forward-translation and back-translation procedure conducted by bilingual mental health experts or professionals with mental health expertise (Piolanti *et al*, forthcoming). All measures and their assessment time points are listed in online supplemental appendix 3 tables S1–S3 and are briefly described below.

As a pragmatic evaluation of a complex intervention, the study includes five co-primary outcomes reflecting key domains of intervention impact. Outcomes such as family functioning and parenting practices are conceptualised as intermediary family processes expected to contribute to downstream adolescent mental health outcomes. Online supplemental appendix 3 figure S2 shows the conceptual model for the current study. Primary outcomes will be evaluated at post-intervention and 6-month follow-up to assess short-term and medium-term effects. Consistent with recommendations for trials of complex interventions, multiplicity will be addressed through prospective specification, transparent reporting and theory-driven interpretation of patterns of effects across the coprimary outcomes and time points.^38^

#### Primary outcomes

The study will assess primary outcomes reflecting key domains of adolescent mental health, family functioning, parenting practices and adolescent and caregiver health-related quality of life. Adolescent emotional problems (internalising) will be assessed using the caregiver-reported version of the Paediatric Symptom Checklist (PSC-17),^39^ internalising subscale. Family functioning will be measured using the caregiver-reported general functioning subscale of the Family Assessment Device (FAD-GF).^40^ Parenting practices will be assessed in caregiver report using the involved parenting and positive parenting subscales of the Alabama Parenting Questionnaire (APQ).^41^ For outcome assessment in the health economic evaluation, we will use information about health-related quality of life of adolescents using the EQ-5D-Y-3L and of caregivers using the EQ-5D-5L.^42^

#### Secondary outcomes

Adolescent emotional problems will be assessed using adolescent-reported symptoms on the Revised Child Anxiety and Depression Scale,^43^ including total, anxiety and depression scores, as well as adolescent-report and caregiver-report versions of the PSC-17,^39^ capturing internalising, externalising and attention problems. Family functioning related to problem solving will be measured using the caregiver-reported problem-solving subscale of the FAD.^40^ Family and parent—child communication will be assessed using the adolescent-reported Child-Parent Communication Apprehension Scale and the Parent–Child Communication Scale completed by both adolescents and caregivers.^44
45^ Additional secondary outcomes include parenting practices reported by adolescents and caregivers, assessed using the APQ, including involved and positive parenting and caregiver-reported harsh parenting.^41^ Caregiver stress will be assessed using the Parental Stress Scale.^46^ Social support will be measured for adolescents and caregivers using the emotional and affectionate support subscales of the Medical Outcomes Study Social Support Survey,^47^ while loneliness will be assessed using age-appropriate versions of the UCLA Loneliness Scale for adolescents Roberts UCLA Loneliness Scale (RULS-8) and caregivers RULS-6.^48
49^ Well-being will be measured for both adolescents and caregivers using the WHO-5 Well-Being Index (WHO-5).^50^ Caregiver psychological distress will be assessed using the Patient Health Questionnaire-9.^51^ Adolescent socioemotional skills, including emotional regulation, problem-solving and interpersonal skills, will be measured using the UNICEF Social Emotional Abilities and Learning tool.^52^ Exposure to emotional maltreatment will be assessed using the caregiver-reported emotional abuse subscale of the adapted ISPCAN Child Abuse Screening Tool, and adolescent experiences of peer violence and bullying will be measured using the Health Behaviour in School-aged Children Peer Violence measure (HBSC).^53–55^ Secondary outcomes related to the economic evaluation include the OxCAP-MH (Oxford CAPabilities questionnaire-Mental Health), an adult self-reported capability well-being instrument, which will be completed by caregivers.^56^ Further self-reported health and social care and broader resource use will be measured using the PECUNIA RUM (v2.0) self-assessed for caregivers and proxy assessed by caregivers for adolescents.^57^ All resources will be costed using national-level unit costs developed based on internationally validated unit costing methodology.^58^

#### Other prespecified outcomes

Other prespecified outcomes comprise measures of participant characteristics, intervention costs, implementation processes and staff outcomes that may influence programme effectiveness. These include food insecurity,^59^ adolescent healthy weight, adolescent and caregiver post-traumatic stress symptoms measured using the Children’s Revised Impact of Event Scale^60^ and the Posttraumatic Stress Disorder Checklist for DSM-5 (PCL-5),^61^ respectively, and adolescent top problems reported by adolescents and caregivers.^62^

Implementation outcomes will include participant and staff experiences. At baseline, staff will report demographic characteristics and prior professional experience. Potential intervention effects on staff will be assessed using pre–post measures of well-being (WHO-5)^50^ and parenting practices (APQ involved and positive parenting subscales).^41^ Staff will also complete weekly self-report measures on programme implementation and any programme modifications or adaptations made during delivery.

During the intervention period (6–8 weeks), implementation outcomes will include assessment of session fidelity using the PLH-FAT, monitoring of PLH session attendance (individual, family and catch-up attendance), and documentation of enrolment rates (individual and family enrolment).^58
63^ Weekly PLH sessions will be video-recorded for supervision and fidelity assessment purposes. A subset of sessions will be independently rated by supervisors using the 27-item PLH-FAT to generate fidelity scores for each intervention group. The fidelity assessment tool and coding guidance will be iteratively refined during rater training to support inter-rater reliability of at least 70% agreement and consistency of ratings across study sites.

Intervention cost data will be collected using centrally maintained consumable cost logs and weekly staff self-report time logs capturing training, delivery, supervision and administrative activities related to intervention implementation. These outcomes will be considered exploratory. Implementation outcomes will be assessed using quantitative and qualitative methods throughout intervention delivery and at postintervention assessment.

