### Study setting

Intervention implementation is conducted in two Eastern European countries, North Macedonia and Moldova, and is supported by two established health networks with prior experience delivering PLH programmes. In North Macedonia, the Institute for Marriage, Family and Systemic Practice (ALTERNATIVA) comprises a network of psychologists, social workers and family therapists engaged in research and education on systemic practice and family psychotherapy. In Moldova, the Health for Youth Association (HYA) supports publicly funded youth clinics that deliver preventive and therapeutic services addressing sexual and reproductive health, psychological well-being, substance misuse and violence prevention.

The intervention is scheduled to be delivered to the intervention group between fall 2025 and summer 2026. In Moldova, implementation will occur in a single wave, while in North Macedonia it will be conducted in two waves, based on the feasibility of recruiting families. This approach is consistent with procedures successfully used in North Macedonia during phase 2 of the FLOURISH project.

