Based on findings from previous phases of the FLOURISH project, recruitment in phase 3 will be expanded to better reach vulnerable families through both education and health system channels. In North Macedonia, this will include training school staff, psychologists, social workers and educational personnel to support recruitment efforts, as well as targeted outreach to families residing in family houses supported by SOS Children’s Village and Albanian-speaking communities. In Moldova, families will be recruited through Youth Klinic (YK) beneficiaries and health-promoting school partners using individual discussions, parent meetings at YKs and schools and informational announcements at YKs. Additional efforts will be made to include Russian-speaking families affected by displacement or regional instability related to the war in Ukraine and residents of the administrative-territorial units on the left bank of the Dniester river, also known as Transnistria.

Intervention staff will include facilitators, supervisors and supporting and coordinating personnel in each country, affiliated with the implementing organisations ALTERNATIVA in North Macedonia and HYA in Moldova. All intervention staff must be at least 18 years old, complete mandatory training, commit to their assigned roles in programme delivery, supervision or assessment, and provide written informed consent. An example of the caregiver informed consent form is provided in online supplemental appendix 2. Facilitators are professionals, some of whom have prior experience in parenting interventions, trained to deliver the PLH programme, lead group sessions and support adolescents and caregivers. Supervisors are senior staff members who oversee facilitators, monitor intervention fidelity and conduct facilitator supervisions and fidelity evaluations. Data assessors are trained research staff responsible for administering standardised assessments and ensuring high-quality, accurate data collection.

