### Randomisation and blinding

This study will involve a multicountry, cluster/group randomised controlled trial of the adapted PLH programme. Clusters will be randomly assigned to either the intervention group or the waitlist control group (see online supplemental appendix 3 figure S1 for the study flow chart). Each group (intervention and waitlist control) will consist of 10 adolescent–caregiver pairs, with a total of 32 groups per country, implemented across 16 sites in North Macedonia and 16 sites in Moldova.

Randomisation will occur at the group level and be based on predefined clusters with two clusters embedded within each geographical region (ie, school or youth clinic A and B). Stratified randomisation with country as the strata will be employed. A total of two sets with 16 sites/clusters will be randomised within each of the countries for a total of 64 sites/clusters overall. In North Macedonia, eligible site/clusters will be primary schools in Macedonian-speaking and Albanian-speaking urban and suburban areas of the Skopje metropolitan region. In Moldova, site/clusters will be Youth Clinics or schools. Across both countries, two clusters (ie, groups) per geographical region will be randomly assigned to either the intervention or the waitlist control condition.

The list of sites/clustered will be provided to the University of Klagenfurt, randomisation will be conducted independently by the University of Klagenfurt and provided to the research coordinators in North Macedonia and Moldova. The random allocation sequence will be generated by the project coordinator at the University of Klagenfurt using a computerised randomisation tool. Participants and data assessors will be blinded during informed consent and baseline assessments. After baseline is completed, participants will be informed of their allocation to intervention group or waitlist. Data assessors will remain blinded during the post and follow-up assessments. Pre, post and follow-up data sent to the analysis team will remain blinded until analyses are completed and shared with the team. To minimise assessment bias, different researchers will be responsible for outcome assessments and process monitoring.

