#### Additional exploratory analyses

Additional exploratory analyses will compare the intervention and waitlist control groups on other prespecified outcomes at baseline, postintervention and 6-month follow-up. Multigroup analyses will be conducted to compare models across countries and demographic subgroups (eg, adolescent and caregiver gender). This analysis may inform and feed into the scale-up strategy in terms of potential coverage and outreach in the general population and inform the budget impact analysis of the intervention.

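### Effects of the programme on staff are to be assessed from pre-post scores with no staff comparison group, so that effect cannot be identified (minor, exploratory outcome)

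*Protocol article*

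**What the plan says.** Under Other prespecified outcomes, the protocol article defines a category of "measures of participant characteristics, intervention costs, implementation processes and staff outcomes that may influence programme effectiveness". Within it, the paragraph on implementation outcomes states: "Potential intervention effects on staff will be assessed using pre–post measures of well-being (WHO-5"), and adds the involved and positive parenting subscales of the APQ. The section later says "These outcomes will be considered exploratory"; that sentence closes the paragraph on cost data, so its reach to staff outcomes is likely but not explicit.

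Under Additional exploratory analyses: "Additional exploratory analyses will compare the intervention and waitlist control groups on other prespecified outcomes at baseline, postintervention and 6-month follow-up".

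On who is randomised, Randomisation and blinding says "Clusters will be randomly assigned to either the intervention group or the waitlist control group", and these clusters are groups of adolescent–caregiver pairs. On who the staff are, Participants and recruitment says "Intervention staff will include facilitators, supervisors and supporting and coordinating personnel in each country"; all of them must complete training and commit to a role in delivery, supervision or assessment.

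**The concern.** The stated target is an effect of the intervention on staff, but the only design described for it is one group measured before and after. For families, the same article handles this properly: the randomised arms are compared in a baseline-adjusted model with time and treatment-by-time terms, so change common to both arms drops out of the treatment effect. Nothing plays that part for staff. Facilitators' well-being or self-reported parenting may shift over the delivery weeks because of workload, the time of year or answering the same questionnaire twice, and a pre-post difference cannot tell this apart from an effect of the programme.

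At stake is what may be concluded about staff. The Statistical analyses section says that estimates of effect, with confidence intervals and exact p values, will be given for the prespecified outcomes. Staff scores sit under a heading of that name, so a staff effect with a p value could be reported without support from the randomised design.

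**Working it through.** The plan gives no sample size, power or error rate for staff outcomes, so there is no figure to reproduce. The main check is textual.

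**1. Is there a staff comparator?**
- *Randomisation and blinding*: the units are clusters of families. Staff are not described as randomised.
- *Participants and recruitment*: only staff with a role in the programme are described. No waiting, untrained or non-delivering staff group appears.
- *Other prespecified outcomes*: staff scores are taken pre and post only. No repeated measurement before delivery is described that could show a background trend.

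No comparator is described, either concurrent or historical.

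**2. Can the general arm comparison supply one?** The analysis under Additional exploratory analyses contrasts the two arms at baseline, post-intervention and 6 months. The arms consist of families, no waitlist staff are defined, and staff have no 6-month measure. Read literally, the sentence covers the category that contains staff outcomes. It cannot be carried out for them.

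**3. What does the pre-post change estimate?** Write the mean change in staff as

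E(post − pre) = programme effect + background change.

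One group measured twice yields one number for this sum. Without a comparator or an assumption about background change, the two terms cannot be separated. A larger sample narrows the interval around the sum and leaves the split unknown.

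**4. Illustration under assumptions.** All inputs below are assumptions, and the plan specifies no such test.
- Staff number: "Each group will be led by two facilitators". There are 32 groups per country, so 64 in all and 32 in the intervention arm; 32 × 2 = 64 facilitators if none leads more than one group. I also use 32. Supervisors and coordinating personnel are not counted.
- Pre-post correlation r: 0.5 to 0.7. The value 0.6 is the article's assumption for families, borrowed here.
- True programme effect: zero. Background change: 0.10 or 0.25 SD.
- Two-sided 5% paired z-test, SE of the standardised mean change = √(2(1 − r)/n).

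At n = 64 and r = 0.6: SE = √(0.8/64) = 0.112 SD. For a change of 0.10 SD, z = 0.10/0.112 = 0.89, and the chance of p<0.05 is Φ(0.89 − 1.96) + Φ(−0.89 − 1.96) ≈ 14%.

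| n | r | SE (SD) | change 0.10 SD | change 0.25 SD |
|---|---|---|---|---|
| 32 | 0.5 | 0.177 | 9% | 29% |
| 32 | 0.6 | 0.158 | 10% | 35% |
| 32 | 0.7 | 0.137 | 11% | 45% |
| 64 | 0.5 | 0.125 | 13% | 52% |
| 64 | 0.6 | 0.112 | 14% | 61% |
| 64 | 0.7 | 0.097 | 18% | 73% |

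The table shows only that a modest background change, if there is one, can pass for an effect. It says nothing about whether such a change will occur.

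**The case against.** The strongest reply is that the sentence does little more than name instruments and timing. It is hedged by the word potential and sits in a data-collection section. Quantitative implementation measures are to be analysed by descriptive statistics, correlation and regression, and no test of a staff effect is set out. The outcomes are exploratory, no hypothesis concerns staff well-being or parenting, and the scale-up modelling is said to draw on effectiveness, cost, cost-effectiveness and stakeholder views. The arm comparison is naturally read as covering outcomes that both arms have; fidelity and session attendance, in the same category, could not be compared between arms either. How a change score is modelled can also be left to the statistical analysis plan.

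Most of this stands, and it is why the point is minor. It does not remove the point. An exploratory label speaks to the strength of evidence and does not provide a comparator, and no modelling choice in the analysis plan can create one that the described design lacks.

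Three stronger readings are tempting, and the documents do not support them:
- *A reader might infer that any change in staff scores will be credited to the programme.* The article states no attribution rule.
- *A reader might add regression to the mean as a source of bias.* It shifts a group's average when the group was selected on extreme scores. Staff are selected on age, training, role commitment and consent.
- *A reader might take the staff interval to span most of a year, from "The intervention is scheduled to be delivered to the intervention group between fall 2025 and summer 2026".* That is the calendar for delivery across the whole trial, with two waves in North Macedonia. One course lasts 7 weeks (the outcomes section gives 6–8 weeks for the intervention period), and nothing says that any staff member's pre-post interval runs from fall to summer.

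**Conclusion.** The point holds as a minor one. The article names an intervention effect on staff as the target and describes only an uncontrolled pre-post change to assess it. That design cannot separate a programme effect from other change over the delivery period, and the planned arm comparison cannot fill the gap because the arms are families. No primary or secondary outcome, hypothesis or sample size is touched.

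The conclusion rests on the text alone: no staff comparator is described. It does not rest on the rates in the table (9% to 18% for a 0.10 SD change, 29% to 73% for 0.25 SD), which depend on assumed staff numbers, correlations and background change and on a test that the plan does not specify. They should not be quoted as error rates of this trial.

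**What to change.** Two changes of wording:

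1. Under Other prespecified outcomes, replace the sentence on staff effects with: *Change in staff WHO-5 and APQ scores from before to after delivery will be reported descriptively (mean change with 95% CI). It will not be interpreted as an intervention effect, because there is no concurrent staff comparison.*
2. Under Additional exploratory analyses, limit the comparison of arms to other prespecified outcomes that are measured in families in both arms.

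The changes can be made in the protocol or carried into the statistical analysis plan, and need no new data. The cost is giving up a causal statement about staff, which the design does not support.
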